#### Relevant concomitant care permitted or prohibited during the trial {11d}

All relevant concomitant care and interventions are permitted during the trial. Many of the people with dementia taking part will be taking medications for dementia symptoms and co-existing long-term conditions as well as receiving health and/or social care services. All prescribed medications and service use will be recorded as part of the CSRI data collection. Participants enrolled in other intervention research studies at the time of recruitment will not be eligible to take part in the study.

#### Provisions for post-trial care {30}

There are no arrangements to provide the intervention to participants after the trial.

### Outcomes {12}

All outcomes will be collected at baseline and 6 and 12 months.

#### Primary outcome

The primary outcome is functioning of the person with dementia assessed using family carer rated Goal Attainment Scaling (GAS) at 12 months follow-up. GAS is valid, reliable, and responsive to change in function in people with dementia living at home up to 12 months [21, 22]. Trained researchers will work with family carers and people living with dementia to set SMART (Specific, Measurable, Achievable, Realistic and Time-bound) goals across domains including: cognition, instrumental activities of daily life/self-care, mood, behaviour, and mobility. Family carers will evaluate ‘performance’ of the person living with dementia (or carer wellbeing if the goal relates to this) on a minimum of three and maximum of five goals set at baseline, on a 5-point scale ranging from ‘much worse’ to ‘much better’ than expected. As people will have different goals and numbers of goals, a summary formula standardises the degree of goal attainment [21], analysed as a change score. We will calculate GAS for people with dementia who have died, using procedures outlined by Gordon et al. [32]. Where death was unexpected, attainment in each domain will be rated as − 2. Where death was expected (we exclude clients who are considered to be in their last 6 months of life, but circumstances can change and we follow-up clients for 1 year), goals will be rated as achieved prior to death.

#### Secondary outcomes

Researchers conducting follow-up assessments are asked to provide their own rating on Goal Attainment Scaling [22, 33].

Family carers are asked to proxy-complete:
Disability Assessment for Dementia Scale (DADS), a standard measure of functional independence (basic and instrumental activities of daily living) [23].DEMQOL proxy, a widely used measure of quality of life of people with dementia [24];Neuropsychiatric Inventory (NPI) [25];CarerQol [26];The brief Dimensional Apathy Scale (b-DAS) [27];Hospital Anxiety and Depression Scale (HADS) [28];Modified Conflict Tactics Scale to measure potentially abusive behaviours [29]Client Services Receipt Inventory (CSRI) [30] including home care, hospitalisations, respite, and all-cause time to transition from home.People with dementia complete, if they are able to:Goal Attainment Scaling [21, 22], andDEMQoL to rate their quality of life [24]

#### Participant timeline {13}

Table 1 details the schedule and timing of assessments. T9 and T14 represent the 6- and 12-month follow-up points respectively. In the intervention group, the 6-8 main intervention sessions occur between 0 and 6 months (time point 0 and t9) and follow-up phone calls to support implementation between T9 (6 months) and T14 (12 months). Process evaluation interviews will be conducted after all the main outcomes have been completed (T15).

**Table 1 Tab1:** Participant timeline through the study

	Study period																
	Enrollment	Baseline and allocation	Post allocation													Final follow-up	Qualitative interviews
Timepoint	-*t*_1_	0	*t*_1_	*t*_*2*_	*t*_3_	*t*_*4*_	*t*_5_	*t*_6_	*t*_*7*_	*t*_8_	*t*_9_	*t* _10_	*t* _11_	*t* _12_	*t* _13_	*t*_14_	*t*_15_
Enrollment																	
Eligibility checks	X																
Informed consent	X																
Allocation		X															
Intervention delivery																	
NIDUS-family Intervention sessions			X	X	X	X	X	X	X	X							
NIDUS-family telephone follow-ups											X	X	X	X	X		
Assessments																	
Participant demographics		X															
Goal Attainment Scaling (GAS)		X									X					X	
Disability Assessment for Dementia Scale (DADS)		X									X					X	
DEMQOL/DEMQOL proxy		X									X					X	
Neuropsychiatric Inventory		X									X					X	
CarerQol		X									X					X	
Brief Dimensional Apathy Scale		X									X					X	
Hospital Anxiety and Depression Scale (HADS)		X									X					X	
Client Services Receipt Inventory (CSRI)		X									X					X	
Modified Conflict Tactics Scale		X									X					X	
Acceptability of intervention (intervention group)																X	
Qualitative interviews (10% of intervention sample)																	X

### Sample size {14}

The sample size calculation is based on the primary comparison of Goal Attainment Scaling change scores at 12 months between the intervention and usual care groups. Assuming a moderate effect size of 0.5 [34], 198 intervention and 99 control subjects are required to detect such a difference at a 5% significance level (2-tailed) with 90% power. The calculation includes an inflation for clustering due to therapist in the intervention arm (intracluster correlation coefficient (ICC) = 0.05 average cluster size = 20) and for up to 15% loss to follow-up [35]. The calculation of sample size was carried out using STATA version 14.

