**Methods:**

A randomised, two-arm, single-masked, multi-site clinical trial involving 297 people living with dementia-family carer dyads. Dyads will be randomised 2:1 to receive the NIDUS-family intervention with usual care (*n* = 199) or usual care alone (*n* = 98). The intervention group will be offered, over 1 year, via 6–8 video call or telephone sessions (or face to face if COVID-19 restrictions allow in the recruitment period) in the initial 6 months, followed by telephone follow-ups every 1–2 months to support implementation, with a trained facilitator.

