### Trial design {8}

The trial is a two-armed, parallel group, single masked, multi-site, superiority randomised controlled trial. Randomisation is blocked and stratified by site using a 2:1 allocation ratio (two dyads are randomised to the intervention group for every one dyad randomised to the usual care group).

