### Assignment of interventions: masking

#### Who will be blinded {17a}

The researchers collecting outcome data are blinded to group allocations. Four-to-six researchers will work in two small teams, and if a researcher delivers the intervention from one team, a researcher from the other team will conduct the outcome assessments for their participants. Clinical supervision will be conducted with the teams separately to avoid unblinding during discussions. It will not be possible to blind trial participants or researchers delivering the intervention to group allocation, nor will it be possible to blind the statisticians analysing the data due to the 2.1 participant allocation ratio, though analyses will not commence until all data are collected and the database has been locked.

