#### Primary outcome analysis

Family carer-rated Goal Attainment Scaling (GAS) global mean scores at 12 month follow-up will be summarised for the NIDUS-family and usual care groups using means with standard deviations. The outcome will be compared between the groups using a three level mixed effects model which allows for intervention arm therapist clustering and also includes a random effect for study site. The treatment effect estimate from this model will be the adjusted difference in mean GAS score which will be reported with a 95% confidence interval and *P* value. Analyses will be carried out based on the intention to treat principle, comparing the groups as randomised regardless of adherence to the intervention.

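### The 90% power assumes about 20 dyads per facilitator, which does not fit the four to six researchers named under masking; if that is the total who deliver, power is about 82–87.5%

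*Protocol article*

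**What the plan says.** The section Sample size {14} of the protocol article fixes the planning figure: "Assuming a moderate effect size of 0.5 [34], 198 intervention and 99 control subjects are required", "at a 5% significance level (2-tailed) with 90% power". It adds an "inflation for clustering due to therapist in the intervention arm (intracluster correlation coefficient (ICC) = 0.05 average cluster size = 20" and an allowance "for up to 15% loss to follow-up [35". The allocation is 2:1.

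The section Who will be blinded {17a} gives the staffing: "Four-to-six researchers will work in two small teams, and if a researcher delivers the intervention from one team", with someone from the other team doing the outcome assessments for those dyads. The people who deliver and the people who assess therefore come from one pool. The sections that describe the facilitators and their training give no other number.

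The primary analysis is a "three level mixed effects model which allows for intervention arm therapist clustering and also includes a random effect for study site", so facilitator clustering enters the primary comparison as well as the sample size.

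The arm sizes also differ by one dyad. The abstract has "usual care (*n* = 199) or usual care alone (*n* = 98", against 198 and 99 in the sample size section; both total 297.

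**The concern.** When clustering arises from the facilitators, precision depends heavily on how many of them there are. For a fixed number of dyads, fewer facilitators mean larger caseloads and a larger design effect in the intervention arm. An average of 20 per facilitator implies 8.4 facilitators for the analysed dyads (168.3/20) or 9.9 for those randomised (198/20). Four to six is well short of either figure, and the document does not connect the two statements.

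At stake is the planned type II error. The protocol sets it at 10%. If four to six people do all the delivery, the protocol's own method gives 12.5% to 17.7%. Both figures are stated in this document, so the mismatch is not a detail left to the statistical analysis plan.

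**Working it through.** **Inputs.** From Sample size {14}: d = 0.5 (SD = 1), two-sided alpha 0.05, power 90%, ICC 0.05 in the intervention arm only, cluster size m = 20, 15% loss, 198/99 randomised. Analysed: n_t = 198 × 0.85 = 168.3 and n_c = 99 × 0.85 = 84.15. From Who will be blinded {17a}: J = 4 to 6 facilitators, taken here as the total and with equal caseloads.

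**Formulae.** DE = 1 + (m − 1) × ICC; SE = √(DE/n_t + 1/n_c); power = Φ(d/SE − 1.960); effect detectable with 90% power = (1.960 + 1.282) × SE.

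**Reproducing the plan's figure.** DE = 1 + 19 × 0.05 = 1.95. Analysed controls needed: (1 + 1.95/2) × (3.242/0.5)² = 83.0. Dividing by 0.85 gives 97.7 controls and 195.3 intervention dyads, 293 in all, against 297 stated. At 198/99 with 15% loss, SE = 0.1532 and power = 90.4%. The stated calculation is therefore sound on its own inputs.

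**Changing only the number of facilitators** (m = 168.3/J):

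| Facilitators J | m (analysed) | DE | SE | Power | Detectable effect (SD) |
|---|---|---|---|---|---|
| 4 | 42.1 | 3.05 | 0.1733 | 82.3% | 0.56 |
| 5 | 33.7 | 2.63 | 0.1659 | 85.4% | 0.54 |
| 6 | 28.0 | 2.35 | 0.1608 | 87.5% | 0.52 |
| 8 | 21.0 | 2.00 | 0.1542 | 90.0% | 0.50 |
| 8.4 (plan, m = 20) | 20.0 | 1.95 | 0.1532 | 90.4% | 0.50 |
| 12 | 14.0 | 1.65 | 0.1473 | 92.4% | 0.48 |

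The stated 90% is recovered at about eight facilitators.

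**Few-cluster version.** The protocol names no degrees-of-freedom method, so this is conditional on a Satterthwaite-type approximation. Write v_t = DE/n_t and v_c = 1/n_c. Then df = (v_t + v_c)² / [v_t²/(J − 1) + v_c²/(n_c − 1)], with power from the noncentral t distribution.

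| Facilitators J | df | Power | Simulated power (40,000 runs) |
|---|---|---|---|
| 4 | 8.1 | 71.7% | 70.5% |
| 5 | 12.1 | 79.0% | 78.0% |
| 6 | 16.4 | 83.2% | 82.7% |
| 8.4 (plan, m = 20) | 27.8 | 88.3% | not run |

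The fair comparator for this table is 88.3%. About 2 points of any gap from 90% come from the df method and not from the facilitator count.

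**Arm sizes.** With 199/98 at m = 20, power is 90.3% against 90.4%. The difference is clerical; 198/99 is the pair that matches 2:1 exactly.

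**The case against.** The strongest reply is that the masking section explains how assessors are kept apart from deliverers and does not count everyone who will ever deliver. Clustering depends on that full count. Recruitment is planned from April 2020 to February 2022, about 22 months, and each dyad is supported for 12 months, so delivery spans about 34 months. The protocol speaks of initial training, which leaves room for later staff. A complement of four to six at any one time is compatible with eight or more over the trial, and eight gives 90.0% (seven gives 88.9%). Four to six per team, 8–12 in all, gives 90–92%. All of this stands, and it makes the result conditional.

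The size at the upper end is also modest: six facilitators give 87.5%, and about 90.7% if nobody is lost, since 15% is stated as an upper limit. In the other direction, unequal caseloads would lower power further.

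A reader might infer that a null result would be misread. That goes too far. The protocol commits to a 95% confidence interval from a model that allows for therapist clustering, and that interval shows the precision achieved whatever power was planned.

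What the reply does not remove is the mismatch. The document mentions neither turnover nor a per-team count, and the plain reading of the only headcount is four to six in total.

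**Conclusion.** The cluster size behind the 90% power and the stated staffing do not fit together as written. If four to six is the total who deliver, with equal caseloads, ICC 0.05 and the full 15% loss, power is about 82–87.5% and the effect detectable with 90% power is 0.52–0.56 SD. With Satterthwaite-type df, which the protocol does not specify, power is 72–83%, against 88% at cluster size 20 on the same basis.

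A reader might conclude that the trial is underpowered as a matter of fact, or set 72–83% directly against 90%. The documents support neither: the first needs a total facilitator count that the protocol does not give, and the second mixes two changes. This is an inconsistency between two sections that should be fixed, not an arithmetic error in the sample size and not a threat to the validity of the analysis. The 199/98 difference is editorial and adds nothing to the point about power.

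**What to change.** Reconcile Sample size {14} with Who will be blinded {17a} by stating the total number of facilitators expected to deliver over the whole trial, including replacements, and their average caseload.

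- If the total is below about eight, restate the cluster size, design effect and power (or the detectable effect) in the sample size section, using the rows above. If a small-sample df method is planned, quote power on that basis and name the method.
- If it is eight or more, whether through turnover or because four to six is per team, correct the masking section to say so and keep 90%.

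Separately, align the abstract's arm sizes with 198/99.

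The cost is wording only. No extra recruitment and no change to the analysis is asked for. In the first case the stated power becomes somewhat less favourable.

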### Recruitment {15}

Researchers will recruit 297 family carer-people with dementia dyads from memory services or older adult mental health services in NHS Trusts and GP practices supported by the Clinical Research Networks (CRNs): North Thames, Thames Valley and South Midlands, North West London, Kent, Surrey and Sussex, and Yorkshire and Humber. We will aim to recruit 10–20 dyads per trust or GP practice area.

Clinicians and research nurses are asked to contact potential participants during the recruitment period. Verbal permission will be sought from the person living with dementia and the family carer (if present) from the identifying clinician/research nurse, and they will contact the researcher either by telephone or secure email to inform them of any interested participants. The researcher will then contact the person living with dementia and their family carer at least 24 h after the participant information sheet (PIS) has been given by the clinician/research nurse in person, 48 h if it has been sent via email, or at least 72 h if it has been sent by post.

A mail out will also be conducted to all potentially eligible participants at participating GP practices. The mail out will contain the relevant PIS and a letter asking the family carer or person with dementia to indicate their interest in participating in the study either by calling a researcher or returning a reply slip. As researchers receive responses, they will contact the person with dementia and their family carer to answer any questions they may have, check eligibility, determine the context of the situation and relationship, and then, if they would like to, make an appointment to elicit informed consent and conduct the baseline assessment.

The study is also advertised through the social media platform Twitter, the NIDUS study website, and the research organisation Join Dementia Research.

### Assignment of interventions: allocation

#### Sequence generation {16a}

Allocations will be obtained through a remote web based system: www.sealedenvelope.com provided by PRIMENT Clinical Trials Unit (CTU) and following PRIMENT Standard Operating Procedures (SOP). The randomisation list will be blocked and stratified by site using a 2:1 allocation ratio (two dyads will be randomised to the intervention group for every one dyad randomised to the control). The 2:1 ratio was selected to help enhance recruitment as more people will receive the intervention than not, and because the intervention is modular and highly individualised. By randomising more people to receive it, we will obtain a greater understanding of the intervention and the types of modules selected.

#### Concealment mechanism {16b}

Randomisation status is concealed on the remote web based system: www.sealedenvelope.com from the researchers conducting outcome assessments. Only the trial manager and the researcher assigned to deliver the intervention are aware of the participant’s allocation status.

#### Implementation {16c}

Researchers will enrol participants and collect baseline data. They will enter the data onto the Sealed Envelope database; then, as soon as data entry is complete, they will instigate the randomisation procedure. Sealed envelope provides the allocation on participant registration.

### Assignment of interventions: masking

#### Who will be blinded {17a}

The researchers collecting outcome data are blinded to group allocations. Four-to-six researchers will work in two small teams, and if a researcher delivers the intervention from one team, a researcher from the other team will conduct the outcome assessments for their participants. Clinical supervision will be conducted with the teams separately to avoid unblinding during discussions. It will not be possible to blind trial participants or researchers delivering the intervention to group allocation, nor will it be possible to blind the statisticians analysing the data due to the 2.1 participant allocation ratio, though analyses will not commence until all data are collected and the database has been locked.

#### Procedure for unblinding if needed {17b}

Researchers conducting the outcome assessments will remain blinded to participant status throughout the study unless this is accidently disclosed by a participant during outcome assessments. The trial manager will be aware of treatment allocation status and will inform clinical members of the study team of allocation status if a serious adverse event occurs. No circumstances are envisaged whereby the researchers assessing outcomes will be purposefully unblinded.

### Data collection and management

#### Plans for assessment and collection of outcomes {18a}

Data is collected at baseline and 6- and 12-month follow-up for all participants (Table 1). Those in the intervention group are asked to complete an additional measure on acceptability of the intervention at the end of the study. Approximately 10% of participants in the intervention group will participate in an additional qualitative interview about their experiences of receiving the intervention. All researchers are fully trained to use the data collection tools. All outcome assessments will be measured using validated questionnaires (please refer to the ‘Objectives’ section of this protocol for a list of validated questionnaires that will be used in this trial).

#### Plans to promote participant retention and complete follow-up {18b}

While face to face delivery is not possible due to COVID-19 restrictions, we will offer a choice of video call options or telephone contact where participants are unable or do not wish to use video call. Participants will be offered a £20 voucher to thank them for their time after each follow-up appointment (baseline and 6 and 12 months and qualitative interview).

#### Data management {19}

Data will be collected from participants manually on trial specific paper case report forms (CRFs) which will then be entered into a web-based clinical data management system, Red Pill, provided by Sealed Envelope through PRIMENT CTU. There is an agreement in place between the sponsor (UCL) and Sealed Envelope to ensure compliance and agreement with clinical trial regulations, GDPR, and data protection laws. Range checks for data values have been built into the database to minimise data entry errors.

Around 20% of GAS assessments and intervention sessions (randomly selected) will be audio-recorded for fidelity checking, and qualitative interviews will be recorded using a password protected recorder. Files will be transferred between a professional transcription service and UCL, UoB, and Anglia Ruskin University (ARU) via a secure server hosted by the transcription service. Audio files will be password protected and stored in separate folders to the transcripts on password-protected computers at UCL, UoB, and ARU and will only be accessible to members of the research team authorised to use them.

#### Confidentiality {27}

Personal data needed to re-contact participants for follow-up assessments and intervention sessions will be held securely on password protected excel spreadsheets on password-protected computers at UCL, UoB, and ARU (all co-applicants on the study). Data will be stored electronically in folders only accessible to the research team. Data collected at baseline and follow-up will be collected on case report forms (CRFs) that will not bear the participant’s name; only the participant’s trial identification number and date of birth will be used for identification, and this will be clearly explained to the participant in the PIS; these will be held securely in locked premises accessible only to the research team. Consent forms will be held electronically on password-protected computers at UCL and UoB. Only members of the research team will have access to these forms.

Audio files from recorded intervention sessions and qualitative interviews will be transcribed and all identifiable information will be removed from the transcripts including any reference to names or places. Audio files will be deleted from the recording device immediately after the safe upload has been confirmed.

#### Plans for collection, laboratory evaluation, and storage of biological specimens for genetic or molecular analysis in this trial/future use {33}

We will not be collecting any biological specimens for this study; therefore, this section is not applicable.

